### 2.5 Statistical Analysis and Power Considerations

Given the baseline ASD prevalence of 27.6 per 1000 (2.76%) among 8-year-old children in the United States [34], the sample size (n = 1000) is designed for feasibility and exploratory signal detection rather than definitive causal inference. The exact power profile and expected case numbers across varying relative risk reductions are detailed in Table 1.

**Table 1. T001:** **Statistical power profile**.

Relative risk reduction	Expected cases (treatment vs. control, n = 500/arm)	Statistical power (Fisher’s exact, α = 0.05)
30%	~9.7 vs ~13.8	10.3%
50%	~6.9 vs ~13.8	27%
70%	~4.1 vs ~13.8	57.2%
80%	~2.8 vs ~13.8	75%

Expected case numbers in the control arm (standard exposure, n = 500) are calculated assuming a 2.76% baseline ASD prevalence (500 × 0.0276 ≈ 13.8 cases), consistent with the 27.6-per-1000 estimate reported among 8-year-old children in the US ADDM Network [34]. Statistical power evaluated via Fisher's exact test (α = 0.05, two-sided) across varying relative risk reductions. ADDM, Autism and Developmental Disabilities Monitoring.

The primary outcome, the composite trajectory score, will be evaluated via linear mixed-effects models adjusting for major confounders. The secondary outcome, binary ASD incidence, will be evaluated via Firth’s penalized logistic regression with exact confidence intervals (Table 1). Given the approximately 4:1 male-to-female ratio in ASD prevalence, exploratory sex-specific analyses will evaluate differential intervention effects.

Longitudinal data will be analyzed via mixed-effects models to leverage repeated observations over time. Additionally, Bayesian statistical modeling will estimate posterior probability distributions for the effect of electromagnetic exposure reduction, a robust methodological approach for limited sample sizes. Collectively, these strategies will identify early developmental divergences and generate the preliminary epidemiological evidence required to justify larger, multi-center trials.

Anticipated attrition was estimated with reference to comparable Italian newborn cohort studies. The NASCITA, NINFEA/Piccolipiù birth cohorts anticipate a 20% loss to follow-up by 24 months, extrapolated from prior experience with the low-burden, passive data-collection protocols embedded in routine pediatric care used by the NINFEA and Piccolipiù cohorts [72]. Active behavioral interventions over a comparable postnatal window have reported considerably higher attrition [73]. Given the higher behavioral burden associated with sustained household EMR-shielding compliance over the same 24-month window, an attrition rate of 20–22% is assumed. Missing data across longitudinal assessments will be addressed using multiple imputation by chained equations (MICE), under a missing-at-random assumption; primary analyses will be repeated as complete-case and available-case sensitivity analyses.

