**Methods and Analysis::**

A prospective observational pilot cohort study (24-month follow-up) proposes to enroll 1000 full-term newborns into two arms: an EMR-reduced cohort (n = 500, rest and sleep-phase Faraday shielding) and a standard exposure cohort (n = 500). Exposure is quantified via radiofrequency (RF)/extremely low frequency(ELF) measurements, proximity analysis, device inventories and wearable dosimetry. The primary endpoint is a continuous neurodevelopmental trajectory score (joint attention, language, electroencephalogram (EEG) mu-rhythm); binary ASD diagnosis (Autism Diagnostic Observation Schedule, Second Edition (ADOS-2), Autism Diagnostic Interview-Revised (ADI-R)) is a secondary, exploratory endpoint. Moreover, an optional genomic screening will evaluate gene-environment interactions within extremely low-frequency electromagnetic field (ELF-EMF) vulnerable pathways, including ASD-associated genes upregulated by RF via bromodomain and extraterminal protein (BET)-mediated epigenetic mechanisms. Analyses will employ risk ratios, Fisher’s exact tests and logistic regression adjusted for confounders; mixed-effects and Bayesian modeling will evaluate longitudinal outcomes and exposure reduction effects. Given a 2–3% baseline prevalence, approximately 20–30 ASD cases are expected. The study is therefore powered for exploratory signal detection rather than definitive causal inference, providing the critical baseline data required to justify and design future confirmatory trials. Sex-stratified modeling will address the 4:1 male-to-female prevalence ratio.

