### 2.3 Outcome Measures and Covariates

Because neurodevelopment during infancy is more sensitively characterized by continuous developmental measures than by a binary diagnostic outcome, the primary endpoint consists of a predefined composite continuous score integrating joint attention (Early Social Communication Scales; ESCS), early receptive and expressive language development (Communicative Development Inventories [CDI] and/or Mullen Scales of Early Learning [MSEL]), and electroencephalographic (EEG) mu-rhythm spectral power (8–13 Hz) [53]. This composite endpoint will be analyzed longitudinally using linear mixed-effects models, thereby maximizing statistical power while accounting for repeated within-subject measurements over the 24-month follow-up period.

A binary diagnosis of Autism Spectrum Disorder at 24 months, established according to ADOS-2, ADI-R, and Diagnostic and Statistical Manual of Mental Disorders, Fifth Edition (DSM-5) criteria, will constitute a prespecified secondary exploratory endpoint. Because the expected number of ASD cases is relatively small, this outcome will be analyzed using Firth’s penalized logistic regression to minimize small-sample and rare-event bias [70].

To estimate the independent association between EMR exposure and neurodevelopmental outcomes, while minimizing potential confounding arising from parental health-seeking behavior and other selection factors, multivariable regression models will be used. These will adjust for predefined covariates, including a standardized parental socioeconomic status index, objectively recorded child screen-time exposure, and baseline parental health anxiety assessed using the Short Health Anxiety Inventory (SHAI). Additional prespecified clinical and perinatal covariates will be incorporated where appropriate.

All neurodevelopmental assessments, including ADOS-2, ADI-R, and EEG acquisition and analysis, will be performed by trained evaluators blinded to cohort allocation in a standardized clinical environment designed to minimize inadvertent disclosure of exposure status. Video recordings and EEG datasets will be independently coded by assessors blinded to study arm, and inter-rater reliability will be formally evaluated and reported.

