### 3.2 Methodological Limitations

Despite the rigorous methodological framework, several limitations inherent to environmental epidemiology must be explicitly acknowledged:

• Observational Design and Confounding: The physical and behavioral nature of household shielding precludes double-blind randomization; a credible sham-shield is technically unfeasible, and mandating this intervention against parental preference over 24 months would drive high, differential non-adherence. Allocation is thus observational, based on parental choice, making cluster-randomized or stepped-wedge designs impractical. Multivariable regression and Bayesian models will adjust for measured baseline confounders (socioeconomic status, parental age, perinatal history), though residual confounding from unmeasured environmental co-exposures (e.g., toxicants) may persist. To detect residual bias, we incorporate two negative controls: ambient sleep-room temperature (negative exposure) and 24-month height-for-age percentile (negative outcome). Lacking randomization, the primary analysis adopts a Target Trial Emulation framework [74], setting time zero at birth and comparing sustained sleep-phase EMR-reduction against standard exposure over 24 months. Time-varying exposure status—validated monthly via sensors and dosimeters—and covariates are used to construct monthly inverse probability of treatment weights (IPTW) and inverse probability of censoring weights (IPCW) to address differential attrition. These dynamic weights feed marginal structural models (MSMs) estimating the per-protocol effect of EMR reduction. Finally, an E-value sensitivity analysis [75] will quantify the minimum strength of association an unmeasured confounder must have with both exposure and outcome to explain away the observed risk ratio. Ultimately, these methods adjust only for measured, time-varying covariates; unmeasured confounding and differential diagnostic bias remain acknowledged design limitations.

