• Dosimetric Complexity and Practical Feasibility: Continuous ambient monitoring, embedded shield-integrity sensors, and wearable dosimeters (see Exposure Control and Environmental Monitoring) provide objective, multi-layered exposure verification, yet quantifying cumulative near-field exposure accurately over 24 months remains technically challenging. A related risk is behavioral: canopy compliance is expected to decline as infants gain nighttime mobility during the second year of life, and sensor hardware may itself degrade or fail over this period. Quarterly in-home verification visits and monthly cross-checks against wearable dosimetry are designed to detect both forms of degradation and prompt corrective action (equipment replacement, re-training); nonetheless, residual under-detection of declining shield fidelity cannot be fully excluded.

• Statistical Power Limits: With an expected cohort of 1000 subjects and a baseline ASD prevalence of approximately 2.76% [34], the study is intrinsically designed as an exploratory pilot. A Fisher’s exact test power calculation (Monte Carlo simulation, 20,000 iterations, n = 500/arm, two-sided α = 0.05) indicates that statistical power to detect relative risk reductions of 30%, 50%, 70%, and 80% is approximately 10.3%, 27.0%, 57.2%, and 75.0%, respectively (Table 1). The study is therefore underpowered even for large effect sizes and is explicitly designed for exploratory signal detection rather than confirmatory causal inference, carrying a non-trivial risk of Type II error. Accordingly, this pilot is designed primarily to generate effect-size and variance estimates for the formal power calculation of a future, adequately powered multi-center confirmatory trial, rather than to support definitive clinical conclusions in its own right.

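### The ASD endpoint is given an interval that Firth regression does not have, and the table cited for it shows only unadjusted Fisher power before attrition

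*Protocol article*

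**What the plan says.** The ASD analysis is described in four places in the protocol article.

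- **Section 2.3** makes ASD diagnosis at 24 months a secondary exploratory endpoint. It chooses Firth's "penalized logistic regression to minimize small-sample and rare-event bias". The adjustment set named there is a socioeconomic index, recorded screen time and the SHAI health-anxiety score, plus further clinical and perinatal covariates that are not listed.
- **Section 2.5** repeats the choice and adds an interval type and a cross-reference: "penalized logistic regression with exact confidence intervals (Table 1"). Table 1 gives expected cases and Fisher's exact test power for four relative risk reductions. It contains no interval and no Firth result.
- **Section 3.2** says how that power was obtained: "Monte Carlo simulation, 20,000 iterations, n = 500/arm, two-sided α = 0.05". It also plans an E-value for the observed risk ratio.
- **The abstract** says: "Analyses will employ risk ratios, Fisher’s exact tests and logistic regression adjusted for confounders". It does not mention Firth and does not say which of these is the analysis of the ASD endpoint.

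Section 2.5 also assumes attrition of 20–22%.

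**The concern.** Firth regression maximises a penalised likelihood. The intervals that go with it are the penalised profile-likelihood interval or a Wald interval, and both are asymptotic. An exact interval comes from another procedure. One candidate is conditional exact logistic regression, which conditions on the sufficient statistics of the other covariates. With continuous covariates such as an SES index, screen time and a SHAI score, almost every infant has a distinct covariate pattern, so the conditional distribution is degenerate or nearly so. The other candidate is an exact interval from a two-by-two table. That interval is unadjusted, and allocation here is by parental choice.

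The sentence in section 2.5 therefore cannot be carried out as written, and the reference to Table 1 points to a different, unadjusted test. With roughly 16 to 22 events, the choice between these intervals can change what is reported. Table 1 also gives readers a power profile for an analysis and a sample size that the study will not have.

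**Working it through.** **Inputs.** Control risk 0.0276 (Table 1 footnote: "2.76% baseline ASD prevalence (500 × 0.0276 ≈ 13.8 cases")). Arm size 500, two-sided α = 0.05, relative risk reductions (RRR) of 30, 50, 70 and 80% (Table 1 and section 3.2). Attrition 20–22% (section 2.5).

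**Step 1: evaluable sample.** 500 × 0.80 = 400 and 500 × 0.78 = 390 per arm.

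**Step 2: reproduce Table 1, then move to the evaluable sample.** Power is the sum, over all pairs of case counts (a, b), of Bin(a; n, 0.0276 × (1 − RRR)) × Bin(b; n, 0.0276), counting only pairs whose two-sided Fisher p-value is at most 0.05. This is enumerated exactly.

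| RRR | Stated | 500/arm, recomputed | 400/arm | 390/arm |
|---|---|---|---|---|
| 30% | 10.3% | 10.3% | 8.2% | 8.0% |
| 50% | 27% | 27.0% | 20.4% | 19.8% |
| 70% | 57.2% | 57.3% | 44.9% | 43.5% |
| 80% | 75% | 75.1% | 62.1% | 60.6% |

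Table 1 is correct for what it describes.

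**Step 3: events.** Total events = n per arm × 0.0276 × (2 − RRR).

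- No effect: 400 × 0.0276 × 2 = 22.1; 390 × 0.0276 × 2 = 21.5.
- RRR 50%: 400 × 0.0276 × 1.5 = 16.6; 390 × 0.0276 × 1.5 = 16.1.

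**Step 4: does the Firth profile interval work here?** Simulation with 780 infants, 600 runs per setting, exposure plus 3, 6 or 9 covariates (assumed independent and normal), odds ratio 1 or 0.5, about 16–22 events. Coverage of the nominal 95% penalised profile-likelihood interval was 95–96% in every setting, and mean bias in the log odds ratio was at most 0.05.

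**Step 5: power of the planned type of test.** Under the same kind of assumption at 390 per arm, a Firth penalised likelihood-ratio test has power of about 23, 51 and 70% for odds ratios of 0.5, 0.3 and 0.2. At this baseline risk an odds ratio is close to a risk ratio: for 0.5, the control odds are 0.0276/0.9724 = 0.0284, half of that is 0.0142, the risk is 0.0140, and the risk ratio is 0.0140/0.0276 = 0.51. So the planned model falls between Fisher at 390 per arm (19.8, 43.5, 60.6%) and the stated figures (27, 57.2, 75%).

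**Step 6: fitted risks from Firth.** The penalised score equation for the intercept gives Σp̂ = Σy + Σh(0.5 − p̂), where the leverages h sum to the number of parameters k including the intercept. Fitted events therefore exceed observed events by roughly k/2. In simulation (780 infants, 400 runs):

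| Slopes | Effect | Observed events | Fitted events | Excess |
|---|---|---|---|---|
| 6 | none | 21.4 | 24.6 | 3.2/21.4 = 15% |
| 6 | RR 0.5 | 16.2 | 19.4 | 3.2/16.2 = 20% |
| 9 | RR 0.5 | 16.0 | 20.5 | 4.5/16.0 = 28% |

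The excess falls on both cohorts and nearly cancels in a ratio. With 6 slopes and an odds ratio of 0.5, the standardised risk ratio was 0.527 from Firth and 0.524 after intercept correction. With 9 slopes it was 0.515 and 0.511.

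**The case against.** The strongest reply is that this is a slip of one phrase. The estimator is fixed twice, consistently, and anyone using Firth would report its profile interval. The endpoint is secondary and exploratory. The article says openly that the study is underpowered, labels Table 1 as Fisher power, and sizes nothing on it. This limits the consequence. It does not rescue the sentence: the interval named belongs to another method, and the table cited for it concerns a third.

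Three stronger readings are tempting, and the documents do not support them.

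- **Too many covariates.** A reader might infer that the model is overloaded. Section 2.3 names only three covariates, so with exposure there are four slopes and 16.1/4 = 4.0 to 22.1/4 = 5.5 events per slope. Adding parental age and perinatal history from section 3.2 gives six slopes and 2.7–3.7. Firth is chosen because events are sparse, and interval coverage held with nine covariates. Rare binary covariates, imputation and weighting were not tested.
- **A distorted E-value.** Section 3.2 wants the E-value to give "the minimum strength of association an unmeasured confounder must have with both exposure and outcome to explain away the observed risk ratio". A reader might carry the 15–28% overstatement of fitted events over to that ratio, but the risk ratio is almost unaffected. Nor does the article say that the ratio will come from Firth fitted probabilities: the E-value is described after the weighted marginal structural models.
- **An abstract that replaces the adjusted model.** The same sentence that names Fisher's test also names adjusted logistic regression. Fisher is an addition there, not a substitute. What is missing is only which analysis is the ASD analysis.

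**Conclusion.** The point holds for the interval, the cross-reference and Table 1. The stated interval cannot be produced from the stated model. Table 1 describes neither the adjusted analysis nor the evaluable sample. At 390–400 per arm, Fisher power is about 8, 20, 44 and 61%, against the stated 10.3, 27, 57.2 and 75%. The largest loss is 12 to 14 percentage points, at risk reductions of 70 and 80%. A Firth test recovers part of this.

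The Fisher figures rest on the article's own risk and attrition, with attrition equal in both arms and only infants with an observed diagnosis counted. The article plans multiple imputation, which could recover some information. The Firth figures rest on assumed independent normal covariates. The article's conclusion that the study is exploratory and underpowered does not change, and for a secondary endpoint the consequence is moderate.

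**What to change.** 1. In section 2.5, replace the interval phrase with: Firth's penalized logistic regression with penalised profile-likelihood 95% confidence intervals. Remove the pointer to Table 1 from that sentence.
2. In the abstract, name this adjusted model as the analysis of the ASD endpoint. Keep Fisher's test, if at all, as an unadjusted description.
3. Restate Table 1 for the Firth model at about 390–400 evaluable infants per arm, stating the assumed covariates. If Fisher figures are kept, give them at that sample size too.
4. If absolute risks or risk differences are taken from the Firth model, apply an intercept correction (FLIC or FLAC).

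The cost is a few sentences and a short simulation. No new data, visits or participants are needed.

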### 2.6 Safety Considerations

The Faraday canopy is a passive, grounded, silver-coated net with no active electrical or electromagnetic emission. Canopy design will comply with standard infant sleep-safety requirements regarding ventilation and entanglement prevention. The ethics committee review (Ethics and Dissemination) will specifically evaluate the canopy’s physical safety profile for infants as an explicit approval criterion prior to enrollment.

## 3. Discussion

The present study protocol translates the Resonant Convergence framework [57] into a prospective epidemiological investigation, shifting from genetic determinism to a dynamic Gene-Environment interaction paradigm to test whether EMR acts as a modulatory cofactor in ASD pathogenesis via ICR detuning of the Ca^2+^-CaM pathway. Although this framework offers coherent multi-scale integration, its applicability to infant connectome development remains theoretically grounded; this pilot study is therefore conceived as an initial *in vivo* test of these biophysical models, not as their presupposition. Crucially, its core public health utility rests on the empirical testing of exposure reduction — independent of ICR/TR validation — as a significant neurodevelopmental divergence between cohorts would constitute a medically vital endpoint irrespective of mechanistic confirmation.

The following sections discuss the expected impact of a positive finding and the inherent methodological limitations.

### 3.1 Expected Study Impact

If the primary hypothesis is supported, this study will yield substantial theoretical and clinical impact. From a bio-physiopathological perspective, as it would provide the first prospective *in vivo* validation of the ICR and Thermomagnetic Resonance (TR) models applied to neurodevelopment. Demonstrating that low-intensity, non-thermal EMFs alter early neuronal synchronization and MNS maturation would validate the hypothesis of electromagnetic epigenetic modulation and support the development of a novel EMR safety protocol for newborns. Specifically, it would confirm the *in vivo* up-regulation of ASD-linked genes (e.g., TBR1, FOXG1) via BET-dependent mechanisms, paralleling recent observations in human cortical organoids [35].

Secondly, from a clinical and public health standpoint, identifying EMR as an actionable, non-chemical environmental trigger during the critical first 2 years would introduce a new primary prevention strategy. Standardized sleep-phase electromagnetic shielding and proactive dosimetric reduction could become highly cost-effective, low-burden, non-pharmacological recommendations for families, particularly those with a baseline genetic susceptibility to ASD, fundamentally altering pediatric environmental medicine guidelines.

### 3.2 Methodological Limitations

Despite the rigorous methodological framework, several limitations inherent to environmental epidemiology must be explicitly acknowledged:

• Observational Design and Confounding: The physical and behavioral nature of household shielding precludes double-blind randomization; a credible sham-shield is technically unfeasible, and mandating this intervention against parental preference over 24 months would drive high, differential non-adherence. Allocation is thus observational, based on parental choice, making cluster-randomized or stepped-wedge designs impractical. Multivariable regression and Bayesian models will adjust for measured baseline confounders (socioeconomic status, parental age, perinatal history), though residual confounding from unmeasured environmental co-exposures (e.g., toxicants) may persist. To detect residual bias, we incorporate two negative controls: ambient sleep-room temperature (negative exposure) and 24-month height-for-age percentile (negative outcome). Lacking randomization, the primary analysis adopts a Target Trial Emulation framework [74], setting time zero at birth and comparing sustained sleep-phase EMR-reduction against standard exposure over 24 months. Time-varying exposure status—validated monthly via sensors and dosimeters—and covariates are used to construct monthly inverse probability of treatment weights (IPTW) and inverse probability of censoring weights (IPCW) to address differential attrition. These dynamic weights feed marginal structural models (MSMs) estimating the per-protocol effect of EMR reduction. Finally, an E-value sensitivity analysis [75] will quantify the minimum strength of association an unmeasured confounder must have with both exposure and outcome to explain away the observed risk ratio. Ultimately, these methods adjust only for measured, time-varying covariates; unmeasured confounding and differential diagnostic bias remain acknowledged design limitations.

• Dosimetric Complexity and Practical Feasibility: Continuous ambient monitoring, embedded shield-integrity sensors, and wearable dosimeters (see Exposure Control and Environmental Monitoring) provide objective, multi-layered exposure verification, yet quantifying cumulative near-field exposure accurately over 24 months remains technically challenging. A related risk is behavioral: canopy compliance is expected to decline as infants gain nighttime mobility during the second year of life, and sensor hardware may itself degrade or fail over this period. Quarterly in-home verification visits and monthly cross-checks against wearable dosimetry are designed to detect both forms of degradation and prompt corrective action (equipment replacement, re-training); nonetheless, residual under-detection of declining shield fidelity cannot be fully excluded.

• Statistical Power Limits: With an expected cohort of 1000 subjects and a baseline ASD prevalence of approximately 2.76% [34], the study is intrinsically designed as an exploratory pilot. A Fisher’s exact test power calculation (Monte Carlo simulation, 20,000 iterations, n = 500/arm, two-sided α = 0.05) indicates that statistical power to detect relative risk reductions of 30%, 50%, 70%, and 80% is approximately 10.3%, 27.0%, 57.2%, and 75.0%, respectively (Table 1). The study is therefore underpowered even for large effect sizes and is explicitly designed for exploratory signal detection rather than confirmatory causal inference, carrying a non-trivial risk of Type II error. Accordingly, this pilot is designed primarily to generate effect-size and variance estimates for the formal power calculation of a future, adequately powered multi-center confirmatory trial, rather than to support definitive clinical conclusions in its own right.

